# The effectiveness of immediate versus delayed tubal flushing with oil-based contrast in women with unexplained infertility (H2Oil-timing study): study protocol of a randomized controlled trial

**DOI:** 10.1186/s12905-023-02385-1

**Published:** 2023-05-06

**Keywords:** Infertility, Fallopian tubes, Fertility work-up, Tubal flushing, Hysterosalpingography (HSG), Oil-based contrast medium, Pregnancy, Live birth, Cost-effectiveness, Randomized controlled trial

## Abstract

**Background:**

In women with unexplained infertility, tubal flushing with oil-based contrast during hysterosalpingography leads to significantly more live births as compared to tubal flushing with water-based contrast during hysterosalpingography. However, it is unknown whether incorporating tubal flushing with oil-based contrast in the initial fertility work-up results to a reduced time to conception leading to live birth when compared to delayed tubal flushing that is performed six months after the initial fertility work-up. We also aim to evaluate the effectiveness of tubal flushing with oil-based contrast during hysterosalpingography versus no tubal flushing in the first six months of the study.

**Methods:**

This study will be an investigator-initiated, open-label, international, multicenter, randomized controlled trial with a planned economic analysis alongside the study. Infertile women between 18 and 39 years of age, who have an ovulatory cycle, who are at low risk for tubal pathology and have been advised expectant management for at least six months (based on the Hunault prediction score) will be included in this study. Eligible women will be randomly allocated (1:1) to immediate tubal flushing (intervention) versus delayed tubal flushing (control group) by using web-based block randomization stratified per study center. The primary outcome is time to conception leading to live birth with conception within twelve months after randomization. We assess the cumulative conception rate at six and twelve months as two co-primary outcomes. Secondary outcomes include ongoing pregnancy rate, live birth rate, miscarriage rate, ectopic pregnancy rate, number of complications, procedural pain score and cost-effectiveness. To demonstrate or refute a shorter time to pregnancy of three months with a power of 90%, a sample size of 554 women is calculated.

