### Outcomes

The primary outcome is time to conception leading to live birth, with the first day of the last menstrual bleeding before a positive pregnancy test within 12 months after randomization. We will assess the presence of this endpoint also at six months after randomization as a co-primary outcome. All outcomes are listed and described in Table 1.

**Table 1 Tab1:** Outcomes and descriptions

**Primary outcome**	**Definition/measurement**
Time to conception leading to live birth measured at 6 months	Calculated from the first day of the last menstrual bleeding before a positive pregnancy test
Time to conception leading to live birth measured at 12 months	Calculated from the first day of the last menstrual bleeding before a positive pregnancy test
**Secondary outcome**	**Definition/measurement**
Biochemical pregnancy	A positive pregnancy test or serum HCG-level greater than 5 IU/L
Clinical pregnancy	Gestational sac visible on ultrasonography
Ongoing pregnancy	Positive heartbeat at 12 weeks of pregnancy on ultrasonography
Miscarriage	Non-vitality on ultrasound or spontaneous loss of pregnancy
Ectopic pregnancy	No intrauterine gestational sac with an ectopic gestational sac and/or persistent serum HCG levels
Multiple pregnancy	Pregnancy of two or more fetuses
Complications after HSG	All adverse events occurring within one month after HSG procedure, for example pelvic infection, intravasation and allergic reaction
Level of pain during HSG	Reported on VAS (scores: 0.0 to 10.0 cm)
Thyroid function after HSG	Serum FT4 and TSH one month after HSG
Used fertility treatments	IUI, IVF, ICSI
Pregnancy complications	E.g. pregnancy induced hypertension, gestational diabetes, still birth
Pregnancy outcomes	E.g. gestational age, pre-term birth, birth weight
Cost-effectiveness	Effectiveness: time to conception leading to live birth Costs: Healthcare perspective: costs for HSG and fertility treatments Societal perspective: healthcare costs, loss of productivity costs and patient costs (care services paid for by the patients themselves) using iMCQ and iPCQ

HCG: human chorionic gonadotropin, HSG: hysterosalpingography. VAS: Visual Analogue Scale, FT4: free thyroxine, TSH: thyroid-stimulating hormone, IUI: intrauterine insemination, IVF: in vitro fertilization, ICSI: intracytoplasmatic sperm injection, iMCQ: Medical Consumption Questionnaire, iPCQ: Productivity Cost Questionnaire

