### Sample size

The time-to-event method was used for the sample size calculation, based on the study of Dreyer et al. [9]. The expected cumulative live birth rate in the control group is 53% with a median time to event of 11 months in the control group. A two-sided log rank test with an overall sample size of 554 subjects achieves 90% power at a 0.05 significance level to or refute a statistically significant effect with a hazard radio of 1.39. It is assumed that 0.32% of the couples switch from one group to the other group. Sample size calculation was done using PASS 15.0.6 (NCSS Statistical Software LCC, Utah, USA).

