### Statistical analyses

The primary analysis will be performed according to the intention-to-treat principle. Continuous variables that are normally distributed will be summarized as means with standard deviation and, if not normally distributed, as medians with an inter-quartile range. Dichotomous data will be reported as proportions with percentages. We will summarize recruitment numbers, lost to follow-up, protocol violations and other relevant data.

The effectiveness of a fertility work-up with a strategy of immediate tubal flushing during HSG versus a strategy of six-month delayed tubal flushing during HSG will be expressed as a rate of live birth with corresponding 95% confidence intervals. Time to pregnancy will be compared in both groups using Cox Proportional-hazards analysis.

Dichotomous outcomes will be analyzed using either modified Poisson regression or logistic regression as appropriate. Continuous outcomes which are normally distributed will be analyzed using linear regression and if outcomes are non-normally distributed negative binomial regression will be used. Although p-values will be reported, the focus will be on providing Risk Ratios for effectiveness with 95% confidence intervals around them as these are more useful in interpreting the findings of the trial.

For losses to follow-up, protocol violations and missing data, we will attempt worst-case scenario analysis to explore the effect of these factors on the trial findings. As a sensitivity analysis, we will explore the effects of missing data on the trial findings using imputation techniques.

Apart from the analysis for the primary outcome – time to conception within twelve months leading to live birth - we will also perform an analysis comparing the time to conception and number of conceptions within 6 months after randomization that lead to live birth. This will allow us to assess the effect of immediate flushing with oil-based contrast as compared to no flushing.

Apart from the intention-to treat analysis, we planned a per protocol analysis. We will write a separate statistical analysis plan that will specify the details of this analysis. SPSS software (IBM) and R software (R Project for Statistical Computing) will be used for all statistical analyses.

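### The article is inconsistent on whether the 6-month endpoint is co-primary or an additional analysis, so the error rate and power of the primary claim depend on the reading taken

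*Protocol article*

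**What the plan says.** The abstract first names a single primary: "The primary outcome is time to conception leading to live birth with conception within twelve months after randomization". Its next sentence reads "We assess the cumulative conception rate at six and twelve months as two co-primary outcomes".

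The Outcomes section also starts from the 12-month endpoint and then adds: "We will assess the presence of this endpoint also at six months after randomization as a co-primary outcome". Table 1 lists both time points under the primary outcome, each as time to conception leading to live birth.

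The Statistical analyses section ranks them differently: "Apart from the analysis for the primary outcome – time to conception within twelve months leading to live birth - we will also perform an analysis". That further analysis is the 6-month comparison, and its purpose is stated: "This will allow us to assess the effect of immediate flushing with oil-based contrast as compared to no flushing". The same section expresses effectiveness as a live birth rate and applies Cox regression to time to pregnancy.

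The Sample size section gives one calculation: "A two-sided log rank test with an overall sample size of 554 subjects achieves 90% power at a 0.05 significance level". Its inputs are a control rate of 53%, a control median of 11 months and a hazard ratio of 1.39. It gives no figure for 6 months.

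**The concern.** Two sections give 6 months primary status and a third withholds it. The article does not say whether one or both endpoints must succeed, and it neither orders the tests nor divides the alpha. This matters most when the two results disagree. Controls are offered flushing after six months, so an early difference could shrink by 12 months, and a positive 6-month result with a negative 12-month one is plausible. The text would then support either conclusion, and in an open-label trial the choice could be made with the data in view. The 6-month comparison also carries the second stated aim, flushing versus no flushing, so its status affects what the trial may claim.

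**Working it through.** **Inputs.** From the Sample size section: N = 554, two-sided 0.05, 90% power, hazard ratio (HR) 1.39, control median 11 months, control rate 53%. From the abstract: 1:1 allocation. Assumptions added here: exponential times and a constant HR. They agree with the stated rate, since 1 − 2^(−12/11) = 53.05% at 12 months. The 0.32% switching is ignored.

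**The plan's own figure.** Schoenfeld events = 4(1.960 + 1.282)² / (ln 1.39)² = 4 × 10.507 / 0.10844 ≈ 388. The 12-month event probabilities are 0.530 (control) and 1 − 0.47^1.39 = 0.650 (immediate), mean 0.590. So N = 388 / 0.590 ≈ 658 (670 by Freedman's formula), not 554. The stated 90% is not reproduced for a two-sided test with 12 months of follow-up. A one-sided 0.05 test would need 546 by Freedman's formula, or 550 with switching, but the text says two-sided.

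**Power per endpoint at N = 554.** Power = Φ(√(events/4) × ln HR − 1.960).

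| Horizon | Control | Immediate | Events | Mean of Z | Power |
|---|---|---|---|---|---|
| 6 months | 0.315 | 0.409 | 200 | 2.33 | 64.5% |
| 12 months | 0.531 | 0.650 | 327 | 2.98 | 84.6% |

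**If either endpoint suffices (0.05 each).** The 6-month events are a subset of the 12-month events, so under the null the correlation of the two log-rank statistics is √(0.3148/0.5305) = 0.770. The bivariate normal probability that at least one |Z| exceeds 1.96 is 0.0798. A 20,000-run log-rank simulation gave 7.9%.

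**If both are required.** The error is at most 5%. Under the planned effect the correlation is √(200.4/326.8) = 0.783, and joint power is 62.7% (62.5% by simulation). If 12-month power is taken as the stated 90%, the 12-month mean of Z is 1.960 + 1.282 = 3.242 and the 6-month mean is 3.242 × 0.783 = 2.54. That gives 72% power at 6 months and 71% jointly.

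**If 12 months is the sole primary.** The error is 5% and power is 84.6% on the stated two-sided inputs.

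**6-month power if the early HR differs** (assumed range, control rate 31.5%):

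| HR in first 6 months | 1.3 | 1.39 | 1.5 | 1.56 | 1.6 |
|---|---|---|---|---|---|
| Power | 45% | 64% | 83% | 90% | 93% |

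**The case against.** Several counter-arguments have force.

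- **A reading without inflation exists.** The abstract and the Outcomes section both introduce the primary outcome in the singular, at 12 months. The Statistical analyses section does the same, and only one test is powered. On that reading the error is 5%. A reader might infer that the error simply is 8%, or the power simply 63%. The article does not support that, because it states neither an either-endpoint nor a both-endpoints rule.
- **A condensed article may leave the decision rule to the full protocol or SAP.** This is fair, and a missing rule alone would not be a finding. What remains is that the article gives 6 months two different statuses, and a SAP can only side with one section against another. The SAP that the article announces is mentioned directly after the per protocol analysis, for the details of that analysis, so it is no evidence of a multiplicity rule.
- **The 63% absorbs a separate defect.** Part of it comes from 554 women giving about 85% rather than 90% at 12 months. This stands, and is why 71% is shown beside it.
- **The 6-month comparison may have a larger effect.** A reader might infer that the trial is underpowered for flushing versus no flushing. The article does not establish this. HR 1.39 was planned for immediate versus delayed flushing, and controls are unflushed in the first six months. The Background cites an odds ratio of 3.54 (95% CI 2.08 to 6.02) for oil flushing versus none. Applied to a 31.5% control rate, the lower limit gives 48.9%, an HR of about 1.77, above the 1.56 needed for 90% power. That odds ratio concerns pregnancy rather than conception leading to live birth, so it is only indicative.
- **The endpoint wording is mostly loose, not three rival endpoints.** Table 1 defines both time points identically, the Follow-up section checks each conception for live birth, and the 6-month analysis is restricted to conceptions ending in live birth. The terms still need aligning.

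**Conclusion.** The concern holds as an unresolved contradiction about the status of 6 months, not as a demonstrated failure of error control. The consequence is conditional: family-wise error of about 8% if either endpoint suffices, joint power of about 63% to 71% if both are required, and 5% error if 12 months is the sole primary. These figures rest on exponential times and a constant HR of 1.39. The 6-month power depends strongly on the early HR, which the article does not give. The 12-month power of about 85% needs only the stated two-sided inputs and a 12-month horizon.

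**What to change.** 1. In the abstract, Outcomes (with Table 1) and Statistical analyses, use conception leading to live birth as the endpoint throughout and give 6 months one status.
2. State a fixed sequence: 12 months is primary at two-sided 0.05, and 6 months is tested at two-sided 0.05 only if 12 months is significant. This holds the family-wise error at 5% and takes no alpha from the 12-month test.
3. In Sample size, restate power per endpoint: about 85% at 12 months with 554 women on the stated two-sided inputs, and at 6 months about 64% at HR 1.39 with the range tabulated above.

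The cost is wording only, with no new participants or data. The small downside is that the flushing-versus-no-flushing claim becomes conditional on the 12-month result, a contrast that may be diluted once controls have been flushed. If the two claims must stand independently, a level of about 0.031 each holds the family-wise error at 5% under the same exponential assumption, at some loss of 12-month power.

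### The sample-size statement claims 90% power to refute as well as demonstrate a three-month gain, but the design has about 81% at twelve months and 58% at six, and no criterion for refutation is given

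*Protocol article*

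**What the plan says.** The Abstract (Methods) gives the purpose of the sample size of 554 women: "To demonstrate or refute a shorter time to pregnancy of three months with a power of 90" per cent. The Sample size section gives the basis: "A two-sided log rank test with an overall sample size of 554 subjects achieves 90% power at a 0.05 significance level", and the sentence continues, with a word apparently lost, "to or refute a statistically significant effect with a hazard radio of 1.39". The control assumptions are: "The expected cumulative live birth rate in the control group is 53% with a median time to event of 11 months in the control group". Crossover is negligible: "It is assumed that 0.32% of the couples switch from one group to the other group".

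The Follow-up section fixes primary follow-up at twelve months. The six-month endpoint shares primary status (Outcomes): "We will assess the presence of this endpoint also at six months after randomization as a co-primary outcome". Statistical analyses describes it as the comparison of flushing with no flushing.

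The same section plans a Cox model for time to pregnancy. It says that p-values will be reported but that the emphasis will be on risk ratios with 95% confidence intervals. No margin, bound or interval criterion is attached to the word *refute*.

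**The concern.** A superiority test has one positive conclusion. Its power describes how often that conclusion is reached when the planned effect is real. Refuting a benefit of the planned size is a different conclusion: the data must exclude that effect, and the relevant probability is calculated under no effect. The article attaches a single 90% to both.

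At stake is how a null result is read. If a trial is said to have 90% power to refute, a non-significant result can be taken as having refuted the benefit even when the confidence interval still contains the effect the trial was sized for. The six-month comparison is the more exposed of the two because it has fewer events.

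**Working it through.** **Inputs.** From the article: N = 554, 1:1 allocation (277 per arm), HR 1.39, two-sided α = 0.05, control 53% with median 11 months, primary follow-up 12 months. My assumptions: exponential control hazard, no dropout, everyone followed for 12 months. The two control figures agree, since a median of 11 months gives 1 − 0.5^(12/11) = 53.1% at 12 months. The three-month gain also matches the HR: 11/1.39 = 7.9 months, a difference of 3.1.

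**1. The plan's own figure (detection, HR = 1.39).**
- Events needed for 90% power (Schoenfeld): 4 × (1.960 + 1.282)² / (ln 1.39)² = 388. Freedman's formula gives 395.
- Treated proportion at 12 months: 1 − 0.47^1.39 = 65.0%.
- Expected events: 277 × (0.530 + 0.650) = 327.
- Power: Φ(ln 1.39 × √327 / 2 − 1.96) = Φ(1.02) = 84.5%. Freedman gives 83.9%, and log-rank simulation gives 84–85%.
- N for 90% power with 12-month follow-up: 2 × 388 / (0.530 + 0.650) = 658, or 670 by Freedman.

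So 554 women do not reproduce 90%. Two variants come within 3% of 554: one-sided Freedman at 90% (546) and two-sided Schoenfeld at 85% (563). Average follow-up of about 15–18 months would give 89–91% power, but the article states twelve. The 0.32% switching makes no material difference.

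**2. Refutation (HR = 1).** Take the criterion as the upper limit of the two-sided 95% interval falling below 1.39. The probability is Φ(ln 1.39 × √D₀ / 2 − 1.96), where D₀ is the event count with both arms at the control rate.

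| | 12 months | 6 months |
|---|---|---|
| Event proportion per arm | 53.0% | 1 − 0.47^0.5 = 31.4% |
| D₀ = 554 × proportion | 294 | 174 |
| ln 1.39 × √D₀ / 2 | 2.82 | 2.17 |
| P(upper limit < 1.39), formula | 81% | 58% |
| Same, simulation (3,000 trials) | 80% | 57% |

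A looser criterion, a one-sided 95% upper limit below 1.39, gives 88% and 70%. Neither endpoint reaches 90% under either criterion.

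**3. Six-month non-significance, if HR 1.39 also held constantly from randomization.** The protocol does not state this assumption.
- Events: 277 × (0.314 + 0.408) = 200.
- Power: Φ(ln 1.39 × √200 / 2 − 1.96) = 64%, so about 35–36% of six-month analyses would be non-significant.
- When the true HR is 1.39, the upper limit falls below 1.39 in only 2.5% of trials. About 33 of those 35–36 percentage points therefore have an interval still reaching 1.39 (simulation: 33 of 35).
- Sensitivity: six-month power is 83% at HR 1.5, 93% at HR 1.6, and about 47% if there is no effect in month one and HR 1.39 afterwards.

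**The case against.** **Nothing says a null p-value will be called refutation.** This is correct. A reader might infer that the trial has a p-value-only decision rule under which every non-significant result counts against flushing. The article does not support that. The log-rank test is the basis for sizing, the planned analysis is a Cox model, and the stated emphasis is on 95% intervals. The wording permits the misreading but does not prescribe it. The interval emphasis is also worded for risk ratios and is not linked to the refutation claim, which concerns time to pregnancy.

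**Detection and exclusion are nearly mirror images.** This largely stands. A design with true 90% detection power (658 women, 388 events under the alternative, 349 under no effect) would exclude 1.39 under no effect about 87% of the time. So at 12 months about 6 points of the shortfall come from the sample size not reproducing 90%, and about 3 from there being fewer events under the null. The claim would be nearly right at 12 months if the detection figure were right. It would still need a stated criterion, and six months remains far short.

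**The 35% at six months is conditional.** A reader might treat it as the trial's miss rate. It is one minus the six-month detection power under an assumed constant HR of 1.39, whereas the 90% statement is built on 12-month inputs. Controls are unflushed until month six, so a larger early HR is plausible. The Background cites an odds ratio of 3.54 (95% CI 2.08 to 6.02) for flushing versus none, for pregnancy rather than live birth. Even its lower limit, applied to 31% in controls, gives an HR of about 1.8 and power of about 99%. The 35% therefore only illustrates the risk. The 58% does not depend on the size of the effect, because it is calculated under no effect.

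**Harm through guidelines.** The Discussion ties guideline change to a positive result only. The article does not say that a null result would change practice.

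**This belongs in the analysis plan.** A detailed interpretation rule may well sit there, and its absence from the article is no fault. A power claim printed in the article that the design does not meet is a different matter.

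**Conclusion.** The point holds as a misstated power claim. The Abstract and the Sample size section give the design 90% power to refute HR 1.39 or a three-month gain, without saying what refutation means. With 277 per arm, 53% control events at 12 months, fixed 12-month follow-up and no dropout, the probability of excluding 1.39 under no effect is about 81% at 12 months and 58% at six. The 90% for demonstrating the effect is also not reproduced from the stated inputs, which give 84–85% at 12 months. Dropout would lower all these figures; follow-up beyond twelve months would raise the 12-month ones. The planned analyses are not themselves wrong. The fault lies in what the sample-size statement promises.

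**What to change.** In the Abstract and the Sample size section, delete the refutation claim and restate the 12-month power to demonstrate HR 1.39 as recomputed from the stated inputs (about 84–85%). If the original calculation used other inputs, such as longer follow-up, state them and reconcile them with the twelve-month window.

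If a refutation conclusion is wanted, state in Statistical analyses or the separate analysis plan, for each co-primary endpoint:
- a benefit of the planned size is refuted only if the upper 95% limit of the Cox hazard ratio (immediate versus delayed) is below 1.39;
- the probability of this under no effect is about 80% at 12 months and 58% at six;
- any other non-significant result is reported as inconclusive.

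The cost is a few sentences, with no extra patients or data. The downsides are a less favourable power figure and some null results having to be reported as inconclusive.
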